## Abstract

**Background:**

In addiction care, urine drug screening tests are recommended to assess psychoactive substances use. While intrinsic diagnostic value of these tests is demonstrated, the consequences of carrying out these tests on opiate maintenance treatment (OMT) have not been established. The main objective will be to assess the impact of on-site urine drug screening tests (OS-UDS) in general practice compared to routine medical care on OMT retention at 6 months in opioid-dependent patients initiating buprenorphine.

**Methods/Design:**

The ESUB-MG study uses a pragmatic, cluster randomized controlled trial design. General Practitioners (GPs) regularly managing patients treated with buprenorphine and consenting for participating will be invited to participate. GPs will be randomly assigned to one of two groups for 6 to 24 months: (a) control group (usual care: standard medical strategy for assessing drug use); (b) interventional group (including 1/ a training session on practice and interpretation of OS-UDS; 2/ the supply of OS-UDS at GPs’ medical offices; 3/ performing an OS-UDS before the first prescription of buprénorphine). GPs will have to include 1 to 10 patients aged 18 years-old or more, consulting for starting treatment by buprenorphine, not opposed to participate. The primary outcome will be OMT retention at 6 months.

**Discussion:**

This randomized interventional trial should bring sufficient level of evidence to assess effectiveness of performing OS-UDS in general practice for patients treated by buprenorphine. Training GPs to drug tests and supplying them in their office should lead to an improvement of opioid-addicted patients’ care through helping decision.

**Trials registration:**

NCT02345655 (first registration May 14, 2014)

## Background

Opioid addiction is currently defined as a “chronic, relapsing disorder” [1, 2]. Mortality of untreated heroin dependence is consistently estimated at 1–3 % per year, at least half of which is because of heroin overdose [3]. Beyond mortality and morbidity, heroin dependence inflicts enormous social and economic costs due to crime, unemployment, relationship breakdown, and the cost of law enforcement. Data from systematic reviews show that methadone maintenance is the most effective treatment in retaining patients in treatment and suppressing heroin use [4, 5]. The systematic review by Mattick et al. demonstrated the efficacy of buprenorphine maintenance treatment, with a lower retention rate than methadone but giving a similar decrease in opiate consumption [5]. The combination of buprenorphine and naloxone (marketed as Suboxone®) was created to prevent the injection of buprenorphine. Nevertheless, its effectiveness in preventing intravenous use of buprenorphine is not yet clear [6, 7].

The management of opiate-dependent patients in France is shared among specialized centres and general practitioners (GPs). Three drugs are available for the maintenance treatment methadone, buprenorphine (approved since 1995) and buprenorphine-naloxone (approved since 2006). Methadone must be initially prescribed by practitioners in specialized addiction centers, whereas buprenorphine and buprenorphine-naloxone should be prescribed by any general practitioner and available through community pharmacies. The number of people receiving maintenance treatment was estimated around 100,000 for high-dose buprenorphine and around 40,000 for methadone in 2010 [8]. Because the availability and the easy access to buprenorphine [9] most of opiate-dependent patients are managed in general practice [10]. Actually, few GPs take care of these patients: they were only 24 % in 2009 to regularly take care of patients under opiate maintenance treatment (OMT) [11]. One of their difficulties is to evaluate the concordance between the patient’s word and his drug use (OMT and other illicit drugs) [12] while associated drug use is frequent (at least one or two thirds of patients under OMT would also consume alcohol and benzodiazepines [13]).

In the field of addiction, assessment of substances consumption is crucial for diagnosis and, even more, for medical management. Nevertheless, this assessment is often difficult as self-reports use to under estimate psychoactive substances’ consumption [14–18]. One Scandinavian study in 2009 [19] compared the assessment by the psychiatrist of drug consumption in an emergency setting to that obtained by a urine drug screening test (UDT); the reference method being chromatography-tandem mass spectrometry. The physician had correctly assessed the consumption of alcohol but the assessment for illicit substances was not so good for other- psychoactive substances. The value of urine drug screening was assessed comparing urine screening tests’ results and chromatography. At the same time, urine drug screening presented a better sensitivity for benzodiazepines, opiates and cannabis. This study clearly showed that physicians’ assessment of psychoactive drug use lead to underestimate the true consumptions, and UDT would be useful in making decisions about treatment.

By contrast, in certain context, patients can overestimate their use of psychoactive substances notably when entering a detoxification program [20].

French guidelines highlight the need to assess opiate dependence for the management of patients taking OMT: screening tests have to be performed before introducing methadone; they are recommended before starting treatment with buprenorphine and during the follow up of both treatments [21]. Methadone prescription guidelines detail the recommended urine tests: a first, mandatory test before starting methadone treatment and later control tests. The first urine test confirms current drug consumption and the absence of methadone intake. Tests are subsequently done once or twice a week during the first 3 months of treatment, then twice monthly. When the patient has transferred to an outpatient setting, tests can be done if the physician considers it necessary. Tests are not obligatory for buprenorphine, but highly recommended. In 2011, French guidelines advised a standardized screening test schedule in the initiation and follow-up of buprenorphine treatment [22].

The drug tests can be carried out by immunochemical methods, either by automated analyzers in the biology laboratory or by drug screening kits. These tests (whether on a laboratory automat or using a commercial kit) are qualitative and have defined thresholds. False negatives exist for cocaine and benzodiazepines in particular, but test quality is intrinsically better for opiate detection (1.9 % false negatives) [23]. Results can be confirmed by the reference method, liquid or gas phase chromatography with mass spectrometry, which gives quantitative measurements [24]. Screening can be done during the patient’s visit, in either a specialized addiction centre or the physician’s office. Laboratory tests, regardless of the method or the biological medium, are reimbursed by the French health insurance system with no limit on their number or time period. In medical offices, immunoassays have been shown to be reliable [25, 26]; nevertheless, on-site urine drug screening (OS-UDS) by commercial kits are not reimbursed by the French health insurance system but some specialized addiction networks in France provide them to their members.

In a recent study performed among a sample of French GPs, only 12.2 % of GPs reported to perform urinary screening tests and in this proportion were counted GPs who reported to use them for other reasons than initiation and follow up of OMT [11]. The main reason for not performing UDS was a lack of knowledge about screening tests [11]. Among the few GPs using tests, the consequence they reported was mainly reinforcing dialogue with the patient. In another study performed in the same area among 1,507 patients initiating an OMT with buprenorphine or methadone, only 2.6 % had at least a drug test reimbursed by the Health Insurance System during their addiction treatment period [27].

Few studies explored the consequences of carrying out these tests on medical management. In the previous cited study, having been drug tested was associated with a better opiate substitution maintenance, with 45 % decrease of drop-outs (95 % CI: 0.38–0.80) [27]. In a retrospective cohort study of methadone users performed through data obtained from a primary care prescription registry in Tayside, Scotland, a history of having urine tested was a protective factor in relation to all-cause mortality with a reduction of 70 % of risk of death (HR 0.33, 0.22 to 0.49) [28]. On the basis of the literature, one would suppose that carrying out UDS would provide an improvement in the management of patients with opioid addiction and positive outcomes for patients such as longer opiate substitution maintenance and its clinical consequences in which a decrease in mortality. However, this hypothesis relies only on observational data, and we cannot rule out confusion bias.

In order to provide more consolidated data on the interest of using UDT in the context of general practice, we propose an interventional trial, which the main objective is to assess the impact of on-site urine drug screening tests in general practice compared to routine medical care on OMT retention at 6 months in opioid-dependent patients initiating buprenorphine. Second objectives are to assess the acceptability of OS-UDS by patients and GPs, to assess patient adherence to buprenorphine and to assess associated psychoactive consumptions.

## Methods/Design

### Study design

The ESUB-MG study is a pragmatic, cluster randomized controlled trial design. Clustering is at the level of the GP. A cluster design is needed as the intervention concerns the GP and as the evaluation concerns the patient. Furthermore, patients of a same GP are more correlated than patients of different GPs.

### Research objectives

This study is designed to assess the impact of on-site urine drug screening tests in general practice compared to routine medical care on OMT retention at 6 months in opioid-dependent patients initiating buprenorphine.

### Study population

#### GP inclusion criteria

Professional criteria: to practice as a GP, to be in activity, to practice in general ambulatory practice (in a medical office).

Patients’ characteristics: to regularly manage patients treated with buprenorphine.

Legal characteristic: to be registered in sector 1 (a registered doctor has an agreement with Social Security and the fees he applies correspond to ‘reasonable and tactful’ tariffs set by the social security system, whereas a non-registered doctor is authorised to charge higher fees. A sector 1 registered general practitioner charges no more than the statutory fee).

Consent for participating to the trial.

#### GPs exclusion criteria

To practice in a group medical office in which another GP has been included in the trial.

#### Patients' inclusion criteria

Aged 18 years-old or more.

To consult for starting buprenorphine or buprenorphine-naloxone (as several periods of OMT exist for a same period, a period of more than 6 months without OMT will be sufficient to consider that a patient starts buprenorphine or buprenorphine-naloxone).

Affiliated to a health insurance scheme.

Not opposed to participate.

#### Patients’ exclusion criteria

To consult for continuing buprenorphine or for another complain related to opiate substitution treatment.To be known and yet managed by the GP for an opiate maintenance treatment.To have started buprenorphine or buprenorphine-naloxone in a specialized centre or in a hospital.To be treated with methadone.To be treated with methadone and asking a switch toward buprenorphine or buprenorphine-naloxone.Not consenting to participate to the study.

### Recruitment

#### GPs recruitment

Six academic general medicine departments and six centers for evaluation and information on pharmacodependence-addictovigilance (CEIP-A) will work in pairs to recruit voluntary GPs within their network of working GPs and through regional addiction networks.

Recently, in France, general medicine was recognized as a specialty with a specific training. Consecutively, academic general medicine departments were developed in each faculty. In 2008, an academic pathway of general medicine was created.

In order to assist the French health authorities, in charge of the monitoring and the scheduling of psychoactive substances with abuse potential, a monitoring system for psychoactive medications abuse consisting of a national network of 13 centers for evaluation and information on pharmacodependence-addictovigilance (CEIP-A) was created in 1990 [29, 30].

In both sources for selection, GPs will be contacted by postal mail comprising a questionnaire for validating inclusion criteria for the GP, and an agreement form for participating to the ESUB-MG study. A pre-stamped return envelope will be included. Monetary compensation is planned for participating GPs as compensation for the time and contribution to the study.

GPs in both groups will receive both oral and written information about study design and conduct (patients’ recruitment, inclusion criteria). Material for data collection will comprise a GP questionnaire on basic demographic information and location, GP information notice (detail on recruitment and study conduct), questionnaire for the inclusion and follow up visit.

GPs agreeing to participate to the study will be randomly assigned to one of two groups: one group with intervention, one control group.

#### Patients’ recruitment

GPs will be requested to include all consecutive patients that would be eligible. Each GP have to include at least two patients within 18 months.

Participant recruitment will commence in March 2016, and patient participation will be completed by August 2018. The planned end date for the trial is December 2019.

### Consent

GPs will inform eligible patients of their involvement in the study and that their medical data will be used for the purpose of the research. As a research on standard care GPs will have to ensure that patient are not opposed to take part to the research.

Patients that would explicitly express their opposition will not be included. Patients who are not opposed to participate but refusing to submit to one or several OS-UDS will be maintained in their group defined by their cluster.

### Randomization

Randomization will be undertaken at the cluster (GP) level. Based on the procedure allocated to GP, all patients within a cluster will be assigned to either intervention or control group.

Randomization of participating GP will be performed after GP’s approval and collecting complete questionnaire including basic demographic information and their location. The randomization list will be generated by an independent biostatistician in the clinical research methodological support unit (Unité de Soutien Méthodologique à la Recherche Clinique USMR) of the University hospital (Centre Hospitalier Universitaire CHU) of Toulouse, France. Clusters will not be randomized all at once (first patients inclusion need to begin whereas GPs’ recruitment will be on-going), thus the allocation for each consecutive participating GP will be obtained from the USMR through a specific website. To avoid contamination bias, no more than one GP could be included in a given medical practice.

### Intervention

Intervention will consist in: 1) a training session for GPs on use and interpretation of OS-UDS; 2) the supply of OS-UDS at GPs’ medical offices; 3) performing an OS-UDS before the first prescription of buprenorphine. GPs will be let free to perform OS-UDS for the follow-up if they judge it necessary.

GP assigned to the intervention group will be visited by a clinical research assistant (CRA) to be trained on the methods for performing test (urinary sample collection and reading of the test results). The training session is expected to last about 1 h, and a written guidance will be provided. Material for testing (OS-UDS) will also be supplied during this session. OS-UDSs will be centrally bought by the CHU de Toulouse and will be provided by the CRA in charge of the training session.

During the consult, GPs of the intervention group will dedicate an average 5 min to perform OS-UDS. Patients will be asked to collect a urine sample at the GP’s medical office. GP will read and communicate the results immediately to the patients. GPs will keep free of their management according to OS-UDS results.

#### OS-UDS characteristics

OS-UDS will be in accordance with positivity threshold recommended by the National Institute on Drug Abuse (NIDA) [31] and the Substance Abuse and Mental Health Administration (SAMSHA) [32]. The SAMSHA increase the threshold for screening opiates in 2008 (2000 ng/mL instead of 300 ng/mL) to avoid false positive to ingestion of poppy-seeds. Nevertheless, many laboratories maintained the threshold of 300 ng/mL to preserve the opiates screening sensibility [33]. Thus, we will use the threshold of 300 ng/mL.

Several substances will be screened through the OS-UDS in our study: buprenorphine, methadone’s metabolite, 2-ethylidine-1,5-dimethyl-3,3 diphenylpyrrolidine (EDDP), opiates, and cocaine. Opiate substitutes should be systematically screened before starting buprenorphine, according to guidelines. Buprenorphine screening is intended to assess adherence to OMT after initiation, whereas opiates are screened to monitor concomitant consumptions over the course of OMT, or to confirm an opiate addiction before the first prescription (which confirms the indication of OMT). Methadone screening is intended to rule out an ongoing treatment by methadone. Cocaine is often consumed with opiates. In France, at least 10 % of patients would be concerned by cocaine consumption while they are treated with an opioid substitute [34, 35], and it is associated with negative outcome. Some patients could request for an OMT being unaware of the indication of these drugs and believing they could be offered such treatment.

Positivity thresholds currently used [31, 32] and that we will use are: buprenorphine: 10 ng/mL ; EDDP (the metabolite of methadone): 100 ng/mL ; opiates: 300 ng/mL ; cocaine: 300 ng/mL.

At these thresholds, sensibility was 80 % (IC 95 %: 55–100) and specificity 99 % [96 – 100] for opiates, sensibility not calculable and specificity 100 % [100–100] for cocaine [19]. In another study, sensibility for buprenorphine with 3 different OS-UDS varied from 88 to 100 % and specificity from 91 to 100 % [36].

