#### Controlled group

Controlled arm will correspond to standard medical strategy for assessing consumptions while prescribing OMT. Excluding OS-UDS, there will be no prohibited procedure. In particular, GPs of the controlled harm are authorized to implement any biological test to ascertain associated substances use, including for instance laboratory testing. However, according to previous data, we can expected that few drug tests should be performed in this control group: 1 to 3 % [11, 27].

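### Methadone treatment is an exclusion criterion, but only the intervention arm routinely tests for it before the first prescription, and the protocol does not place inclusion before the test: a risk of selection after allocation

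*Protocol article*

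**What the plan says.** All references are to the protocol article.

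- **Exclusion.** Patients’ exclusion criteria lists current methadone treatment, and separately "To be treated with methadone and asking a switch toward buprenorphine or buprenorphine-naloxone".
- **Entry.** Patients' inclusion criteria asks the patient "To consult for starting buprenorphine or buprenorphine-naloxone". Neither list requires a positive opiate screen or test-confirmed dependence. Research objectives names the population as opioid-dependent patients initiating buprenorphine.
- **Order of events.** Under Randomization, the GP is the randomised unit and is allocated one at a time. Under Patients’ recruitment, the GP then includes all consecutive eligible patients.
- **Test in the intervention arm.** The third component under Intervention is "performing an OS-UDS before the first prescription of buprenorphine". OS-UDS characteristics gives its purposes: "Methadone screening is intended to rule out an ongoing treatment by methadone", and the opiate screen serves "to confirm an opiate addiction before the first prescription (which confirms the indication of OMT").
- **Control arm.** Controlled group states "Excluding OS-UDS, there will be no prohibited procedure". Laboratory testing is therefore allowed, but drug tests are expected in only 1 to 3 %.
- **Safeguards.** Consent keeps patients who refuse an OS-UDS in their cluster's group. Statistical analysis analyses patients by their GP's allocation, whether tested or not.

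**The concern.** Whoever applies the exclusion criterion knows the arm, and the information available for applying it differs by arm. An intervention GP who sees a positive EDDP result before prescribing has a listed reason to declare the patient ineligible. A control GP facing the same patient will usually have only the history and may include the patient.

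That would be selection after allocation, produced by the intervention itself. Patients who never enter leave no data, so neither the intention-to-treat rule nor the planned covariate adjustment could bring them back. If those left out would have had poorer retention, the intervention arm would look better without any effect on care.

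Using a result to guide care after inclusion is a legitimate part of the effect under study. Using it to decide who is included is not.

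**Working it through.** **Does the text close the gap?**

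| Provision | What it covers | What it leaves open |
|---|---|---|
| Consecutive inclusion (Patients’ recruitment) | Patients who are eligible | For methadone, the test can change who is judged eligible |
| Refusers kept (Consent) | Patients not tested | Patients tested with a positive EDDP result |
| Freedom of management (Intervention) | Care after the result | Whether a result can undo or prevent inclusion |
| Intention to treat (Statistical analysis) | Patients already included | Patients never included |

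No section puts inclusion before the test. An opiate-negative patient still meets every listed criterion, so for that patient the risk is only informal non-inclusion. An EDDP-positive patient meets a listed exclusion.

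**Planned sample size, as a check of the inputs**

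Inputs from Sample size calculation: retention 36 % and 50 %, α = 0.05 (two-sided assumed, since the article does not say), power 80 %, cluster size 2, intra-cluster correlation 0.0279.

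- Inflation factor: 1 + (2 − 1) × 0.0279 = 1.0279.
- Patients per arm without clustering, two-proportion formula: 196.
- With clustering: 196 × 1.0279 = 201.5 patients, or 100.7 clusters per arm.

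The stated 100 clusters and 200 patients per arm are reproduced closely. Power at 200 per arm is 79.9 %.

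**Size of a possible filter (illustration)**

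Assume no true effect. Retention is 0.36 in the control arm, which keeps everyone. A share x of the same patients is left out of the intervention arm only, and they would have had retention r. The document gives neither x nor r.

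- Apparent intervention retention: p = (0.36 − x·r) / (1 − x).
- Spurious difference: d = p − 0.36.
- Effective size per arm: 200 / 1.0279 = 194.6.
- Standard error: √[(0.36 × 0.64 + p(1 − p)) / 194.6].
- Rejection rate: two-sided normal test at 5 %.

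| x | r | p | d (points) | Share of 14 | Rejection rate |
|---|---|---|---|---|---|
| 5 % | 20 % | 0.368 | +0.8 | 6 % | 5.3 % |
| 5 % | 10 % | 0.374 | +1.4 | 10 % | 5.9 % |
| 10 % | 20 % | 0.378 | +1.8 | 13 % | 6.5 % |
| 10 % | 10 % | 0.389 | +2.9 | 21 % | 9.1 % |
| 15 % | 20 % | 0.388 | +2.8 | 20 % | 8.9 % |
| 15 % | 10 % | 0.406 | +4.6 | 33 % | 15.4 % |
| any | 36 % | 0.360 | 0 | 0 | 5.0 % |
| 5 % | 50 % | 0.353 | −0.7 | −5 % | 5.3 % |
| 15 % | 50 % | 0.335 | −2.5 | −18 % | 8.0 % |

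One line in full, x = 0.15 and r = 0.10: p = (0.36 − 0.015) / 0.85 = 0.406; d = 0.046; standard error 0.049; d divided by its standard error is 0.93, so the two-sided rejection rate is 15.4 %.

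**The case against.** The best defence is that the article treats the test as care given during participation. Refusers stay in their group, the analysis includes patients whether or not they were tested, the test is listed as a component of the intervention, and no sentence says that a result removes anyone. On that reading inclusion comes first, and a condensed article need not spell out the visit sequence. This has weight as a sign of intent. It does not settle the case at issue: those passages deal with untested patients, and an EDDP-positive patient falls under a written exclusion. Applying the criteria as they stand is enough to create the asymmetry.

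Other objections stand and limit the point:

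- A reader might infer that the arms will differ at baseline. The document supports only a risk, because the order of inclusion and test is not stated.
- A reader might infer that confirming the indication is also an eligibility rule. It is a stated clinical purpose of the test, not a listed criterion.
- A reader might infer that control patients are judged on history alone. Laboratory tests are allowed there, so the asymmetry is near-complete, not absolute.
- A reader might infer that the bias must favour the intervention. Primary outcome counts medically prescribed methadone as retention, including from another practitioner in connection with the treating physician, and the Background reports a lower retention rate with buprenorphine than with methadone. Filtered methadone patients could therefore have retention at or above 36 %.

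**Conclusion.** The point holds as a design risk centred on methadone. Eligibility is judged with knowledge of the arm, one exclusion criterion is routinely tested in one arm only, and the text lets the result bear on inclusion. If that happens, no later analysis can undo it.

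The size and the sign are not known from the document. The range of +0.8 to +4.6 points, with type I error of about 5.3 to 15 %, rests on an assumed 5 to 15 % filtered and an assumed 10 to 20 % retention among them. The filtered share would be smaller if only EDDP-positive patients are affected. The lower end is negligible; the upper end is a third of the planned difference. The stronger reading, a certain baseline imbalance in favour of the intervention, is not supported.

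**What to change.** Four additions to the protocol:

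1. Assess eligibility, including methadone treatment, on the same pre-test information in both arms.
2. Register inclusion before any OS-UDS sample is taken, for example on the website already used for GP allocation.
3. State that no OS-UDS result removes an included patient from the primary analysis, extending the existing rule for refusers.
4. Report by arm the included patients who never started buprenorphine.

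The cost is one registration step at the first visit. Patients found to be on methadone after inclusion stay in the analysis set, which may slightly dilute the effect. Sample size does not change, and management after the result stays with the GP, as the protocol already states. The change must be in place before patients are included, because patients left out unrecorded cannot be recovered.
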